#### Introduction – Statement of the Problem

Pregnancy, childbirth, and motherhood are among the most important events in a woman's life and represent the pinnacle of creative artistry and manifestations of divine power (1,2). The period of pregnancy and beyond is a crucial part of family existence and holds a special place in the social life of a community (3) the physiological transition from pregnancy to motherhood signifies a profound physical and psychological change in a woman. This change impacts all bodily systems and can deeply influence women's emotions, behaviors, and thoughts, leading to heightened emotional sensitivity towards psychological stimuli, changes in feelings and attitudes towards children, and better adaptation to the maternal role, affecting future pregnancies and childbirth as well. (4-7)

Any deviation from the natural course of these changes, whether physical or psychological, can create problems for the mother and subsequently for the family. (8) failure to complete the pregnancy process, including miscarriage and stillbirth, can evoke

feelings of failure and grief in women. Grief and mourning, like death and other fundamental issues, are realities of life. An issue that humans consistently face, and sometimes this confrontation occurs at a young age due to pregnancy loss. (8,9) The natural stages of grief include shock and denial, increased awareness (feelings: grief, guilt, anger. Searching, bargaining), perception of the issue (depression, indifference, physical changes), and problem resolution (resilience and annual ceremonies). Healthy mourning is crucial. Because mourning significantly contributes to maintaining balance or tranquility in an individual's life. Essentially, mourning helps individuals recover from the impact of major and minor losses experienced in life. Failing to go through the mourning process naturally may lead to psychological and even physical harm in women. In such cases, feelings of worthlessness and negative body image are felt by women. Stronger feelings of guilt, self-blame, anger, fear, sorrow, and grief emerge more intensely in these women. Beliefs, moral values, and the desire for motherhood become conflicted due to experiencing this loss, leading to a psychological turmoil that results in various mental disorders, including depression, anxiety attacks, suicidal thoughts, sexual dysfunction, sleep disturbances, reduced self-esteem, eating disorders, and difficulties in establishing relationships with other children, ultimately affecting the quality of life. On the other hand, women who have experienced unsuccessful pregnancies such as miscarriage and stillbirth are more likely to be at risk of anxiety and reduced quality of life compared to women without this experience. Various studies have described a high prevalence of anxiety and depression symptoms following perinatal childbirth. (10-13)

One of the most effective ways to combat anxiety and depression is through non-pharmacological methods. Studies have shown that educational and skill-building interventions are effective in reducing depression and can improve the quality of life for mothers. (24) Recently, the use of complementary therapies in treating depression has been under scrutiny. One of the newest and most effective complementary methods is art therapy, whose functions in addressing mental health problems have been confirmed. (25) In recent years, art therapy has gained a special position in the field of treatment as a branch of modern medicine. Some branches of this therapy, such as music and painting, have become more popular in our country. Art therapy is defined as "the use of artistic materials to express and empower the patient through recognizing and resolving their inner conflicts in the presence of a trained art therapist." In art therapy, patients do not

need prior skills or experience in art; rather, through creating artistic works and reflecting on the product and process, they increase their self-awareness and positive emotions, enhancing self-confidence. (27) Art therapy requires attention to patients' psychological needs, interpretation, the need for freedom, expression of existence, and tranquility. Therefore, it does not focus on the details of artistic skills but rather on the role of psychotherapeutic and therapeutic approaches in their activities and artistic productions. Art therapy is widely used for the treatment of mental disabilities, learning disorders, academic failures, anxiety, depression, and obsessive-compulsive disorder. The use of painting, sculpting, photography, collage, music, performance, and poetry form various types of art therapy, presented under titles such as music therapy, drama therapy, narrative therapy, and painting therapy. (28) Art therapy raises awareness of suppressed emotions and reveals them through created images. It is utilized in various groups for controlling stress, anxiety, depression, fear, and improving the quality of life, with focus areas in women and maternal health including depression in menopausal women, breast cancer patients, and postpartum depression. (29-33)

Considering that the responsibility of fertility health service providers is to pay attention to all aspects of fertility health, its process, and function, it seems that in the pursuit of this matter, dealing with the issue of grief and considering the consequences of this phenomenon has not received enough attention in assessing health services. This type of care is lacking in both the perspective of service providers and patients. On the other hand, given the international focus on empowering women to take care of themselves, which has been a major focus in recent years, facilitating women's mental well-being is also considered an important goal of maternal care. (9,34) Healthcare professionals play a significant role in creating positive changes in parents to prepare them for pregnancy and healthy parenting in the future. (35)

Therefore, considering the burden of grief after miscarriage and the likelihood of it progressing towards depression, as well as the current interest and inclination of society towards alternative and non-drug therapies, and the limited research in this area, the necessity of conducting such important and practical research seems inevitable

#### **Implementation Method:**

**Study Type:** The present study is a parallel randomized clinical trial involving 60 mothers (30 in the intervention group and 30 in the control group) who attend the hospitals of Tehran University of Medical Sciences following pregnancy loss. Individuals who meet the inclusion criteria, including a history of recent miscarriage or stillbirth within the last 6 weeks, having at least basic literacy skills, willingness to participate in the study, confirmation of grief using the PGS questionnaire, and residing in Tehran, will be enrolled in the study. At the beginning of the visit, the Perinatal Grief Scale (PGS) will be completed by the participants. Those scoring 92 or higher on the total grief score, or 34 or higher on the active grief or 30 or higher on the difficulty coping subscale, or 27 or higher on the despair subscale, indicating high levels of grief, will be included in the study.

**Randomization Method:** This will be carried out using a block randomization method. Four-person blocks are selected so that Group A will be the intervention group and Group B will be the control group. Each of the six possible scenarios will be written on separate cards, numbered from one to six. The numbers will then be written on paper, randomly selected, until the expected number of samples is complete. The concealment of the sequence will be done using sealed envelopes, each containing one of the designated letters in order, sealed, and given to the researcher. The randomization and concealment process will be performed by a statistical consultant.

**Blinding Procedure:** Due to the nature of the intervention, blinding is not feasible. Subsequently, participants will be informed about the study and will complete an informed consent form. Demographic, grief, anxiety, and quality of life questionnaires will be completed by them. The selected samples will undergo four 90-minute sessions of art therapy and pottery weekly for two weeks according to the designed program detailed below, and anxiety and grief questionnaires will be completed after two sessions of art therapy and at the end of the intervention. Eight weeks after the intervention, the questionnaires will be completed again. During the intervention period, the control group will not receive any art therapy interventions, except for routine medical care following pregnancy loss. To ensure research ethics, all participants will be assured of the confidentiality of the research results. Additionally, after the intervention period, a condensed intervention (2 sessions) will be offered to the control group if the individuals are willing. To combat Miss to follow up issues, participants will be reminded of their class attendance one day before each art therapy session through SMS messages. The completion of questionnaires eight weeks after the intervention will be done electronically.

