4. State-Trait Anxiety Inventory – A self-report psychometric scale measuring two distinct but related concepts of anxiety. Situational anxiety refers to consciously perceived emotional situations causing tension, fear, restlessness, worry, and increased nervous system activity. Personal trait anxiety is individual differences in the disposition to perceive or evaluate stressful situations as threatening or dangerous. Responses to these situations lead to increased anxiety (Lotfi Afshar, 1997).

Initially, women will complete the grief questionnaire, and if individual grief is confirmed, they will be included in the study. The intervention group will receive two sessions per

week, totaling four 90-minute art therapy sessions following a designed protocol. The participants will complete the anxiety, grief, and quality of life questionnaires are completed by participants at the beginning of the study. After 2 weeks of intervention and at the end of the intervention, the grief and anxiety questionnaires are completed again. Eight weeks after the intervention, all three questionnaires will be completed by participants. Upon entry into the study, participants will respond to the quality-of-life questionnaire. They will also respond to the quality-of-life questionnaire with a 4-week interval from the end of the intervention, both before and after the intervention, with a 2-week interval between assessments. The scores before and after the intervention will be compared using paired t-test.

No interventions will be made for the control group during the study period. However, after this time and for ethical considerations, if participants in the control group desire, a more condensed session (2 sessions) with the same content will be held for the control group.

Registration General, Specific, and Practical Objectives Main Objectives of the Plan:

- Determining the effect of art therapy on anxiety and quality of life following pregnancy loss in women attending hospitals affiliated with Tehran University of Medical Sciences in 2019.

Subsidiary Objectives of the Plan:

- Comparing the average grief score following pregnancy loss in the intervention and control groups at the beginning, after two intervention sessions, at the end of the intervention, and 8 weeks after the completion of the intervention in women attending hospitals affiliated with Tehran University of Medical Sciences in 2019.

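### The protocol gives two different limits on when controls may receive art therapy, and the looser one permits it before the 8-week questionnaires

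*Protocol*

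**What the plan says.** Two places in the protocol set the rule for controls.

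- **Summary of Implementation Method and Analysis Approaches:** "No interventions will be made for the control group during the study period. However, after this time and for ethical considerations", followed by the statement that, for those who want it, "a more condensed session (2 sessions) with the same content will be held for the control group". The term for the barred period is not defined, but the sentence comes after the description of assessments that run to eight weeks after the intervention.
- **Implementation Method, Blinding Procedure paragraph:** "During the intervention period, the control group will not receive any art therapy interventions", apart from routine care, and later "after the intervention period, a condensed intervention (2 sessions) will be offered to the control group if the individuals are willing". The same paragraph describes the intervention as "four 90-minute sessions of art therapy and pottery weekly for two weeks" and sets the last assessment: "Eight weeks after the intervention, the questionnaires will be completed again".

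The subsidiary objectives compare the groups on grief and on both anxiety scores at baseline, after two sessions, at the end of the intervention and eight weeks later. They compare quality of life only at baseline and eight weeks after the intervention. The trial has "60 mothers (30 in the intervention group and 30 in the control group").

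**The concern.** The two limits end at different times. Under the summary, the control arm appears to stay untreated until follow-up is over. Under the Implementation Method, the bar lapses when the two-week course ends, and nothing holds the offer back until the last questionnaires are in. Staff who follow the detailed section could treat controls during follow-up without breaching it.

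If that happens, the 8-week contrast no longer compares art therapy with routine care. It compares the full course with a mixture of routine care and a condensed form of the same therapy. Attendance is by choice, so the treated controls would be self-selected. Excluding them or adjusting for attendance would give up the protection of randomisation. Quality of life is one of the two outcomes named in the main objective, and the 8-week comparison is the only post-baseline one its subsidiary objective lists.

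**Working it through.** **1. Timeline, counted from the start of the intervention**

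- Intervention: weeks 0 to 2.
- Last questionnaires: 2 + 8 = week 10.
- Bar on art therapy for controls under the Implementation Method: ends at week 2. The offer is open from then, with no stated start.
- Bar under the summary: ends with the study period. If that period includes the last questionnaires, which is an inference from where the sentence stands, the bar ends no earlier than week 10.
- Window in which the two sections differ: weeks 2 to 10.

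**2. Which comparisons fall after the bar lapses**

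| Outcome | After two sessions | End of intervention | 8 weeks after |
|---|---|---|---|
| Grief | not affected | not affected | exposed |
| Anxiety (both scores) | not affected | not affected | exposed |
| Quality of life | not compared | not compared | exposed |

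The summary also has an unclear sentence about a 4-week interval for quality of life. It does not remove the exposure at 8 weeks.

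**3. Illustration of size**

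There is no figure of the plan's own to reproduce: the protocol gives no effect size, SD, significance level or power for its 60 participants. From the documents: 30 per arm. Assumed: a two-sided test at 0.05, equal SDs, complete follow-up, a true undiluted 8-week effect that 30 per arm detects with 80% power, control uptake *u*, and a fraction *r* of the full effect carried by the two sessions. Uptake is taken as unrelated to outcome, and the SD as unchanged by dilution.

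Two-sample t-test, 58 degrees of freedom, critical value 2.002, noncentrality d × √(30/2). Solving for 80% power gives d = 0.736 SD (noncentrality 0.736 × 3.873 = 2.85). The diluted effect is 0.736 × (1 − u × r).

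| Uptake u | r = 0.5: diluted d | Power | r = 1: diluted d | Power |
|---|---|---|---|---|
| 0% | 0.736 | 80% | 0.736 | 80% |
| 30% | 0.736 × 0.85 = 0.625 | 66% | 0.736 × 0.70 = 0.515 | 50% |
| 60% | 0.736 × 0.70 = 0.515 | 50% | 0.736 × 0.40 = 0.294 | 20% |
| 100% | 0.736 × 0.50 = 0.368 | 29% | 0 | no difference left |

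Both values of r are shown because the sessions are half in number but are described as having the same content, and the protocol does not say what effect they would have.

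**The case against.** The best reply is that the two sections are compatible. Any date after the study period is also after the intervention period, so one schedule satisfies both, and if the stricter summary governs, the 8-week data stay clean. This stands in part: the safe reading is available, and nothing in the protocol shows an intention to treat controls early. It does not settle the matter, because the detailed section does not require that schedule, no sentence says which section prevails, and the summary's barred period is undefined.

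Three stronger readings are tempting and are not supported.

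- A reader might infer that controls are to be treated straight after week 2. The text says only that the offer comes after the intervention period. It allows early sessions without scheduling them.
- A reader might infer that controls would get half the programme, and so half the effect. The summary describes two condensed sessions with the same content. Half is true of the session count only.
- A reader might infer that the whole trial is compromised. The grief and anxiety comparisons after two sessions and at the end of the intervention come before any offer to controls, and anxiety is the other outcome in the main objective.

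It is also fair to say that the power figures are hypothetical. They are, and the finding does not depend on them. Nor can the matter be left to a statistical analysis plan: the timing of an offer of treatment is a rule of conduct, and analysis cannot restore an untreated control arm.

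**Conclusion.** The point holds as an internal contradiction that leaves the 8-week comparison unprotected. As written, the Implementation Method permits control sessions in the eight weeks before the last questionnaires, while the summary bars them for the study period. That the summary's bar covers the 8-week assessment is a reasonable inference, not a stated fact. Contamination is possible, not planned.

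The exposure is limited to the 8-week contrasts. It weighs most on quality of life; for grief and anxiety it touches only the last of three post-baseline comparisons. On the assumptions above, the loss ranges from none, if no control attends early, to the whole contrast, if all attend and the condensed sessions work as well as the full course. The protocol gives no basis for choosing a point in that range.

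**What to change.** Reconcile the summary and the Implementation Method to one timing of the offer to controls, expressed relative to the control arm's 8-week questionnaires. Which timing to adopt is for the investigators. Whichever it is, the protocol should state its consequence: the 8-week contrast estimates art therapy against routine care only if no control has attended a session before completing those questionnaires. Record the date of every session a control attends, so that any overlap with follow-up can be seen and reported.

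The cost is one sentence and a date field, with no additional participants or visits.

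### The only named measure against loss to follow-up is a session-attendance SMS, which acts on the art arm alone and is not aimed at questionnaire return in either arm

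*Protocol*

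**What the plan says.** The Blinding Procedure paragraph of the protocol's Implementation Method section gives one measure, and the same sentence states that its purpose is to counter loss to follow-up: "participants will be reminded of their class attendance one day before each art therapy session through SMS messages". A further sentence deals with the last assessment: "The completion of questionnaires eight weeks after the intervention will be done electronically". It gives a mode of completion and describes no reminder.

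The Summary of Implementation Method and Analysis Approaches gives the intervention group two sessions a week, "totaling four 90-minute art therapy sessions following a designed protocol". Over the same period, according to Implementation Method, "the control group will not receive any art therapy interventions, except for routine medical care following pregnancy loss".

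Controls may later take a shortened course. The two sections time it differently. Implementation Method says that "after the intervention period, a condensed intervention (2 sessions) will be offered to the control group if the individuals are willing". The Summary says "No interventions will be made for the control group during the study period" and places the shortened course after that time.

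The subsidiary objectives compare grief and both anxiety scores between arms at baseline, after two sessions, at the end of the intervention and 8 weeks later. They compare quality of life before the intervention and 8 weeks after it. On the last assessment the Summary says: "Eight weeks after the intervention, all three questionnaires will be completed by participants".

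**The concern.** A measure against loss to follow-up should protect the outcome data, and should do so equally in both arms. This one is triggered by a session and concerns attendance at that session. Women in the art arm are reminded and brought together around the first two post-baseline assessments. The protocol describes nothing comparable for controls. For the 8-week form it describes no prompt for anyone.

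Women enter because their grief score is high, they know their allocation, and every outcome is self-completed. Whether a woman returns a form may well depend on how she feels, which is the outcome itself. If return also differs between arms, the women who answer are no longer the groups that were randomised. Distressed non-responders in the control arm would make controls look better than they are; recovered non-responders would make them look worse. Analysis can only partly repair this, because the missing scores are not observed. Prevention belongs in trial conduct, which the protocol addresses here explicitly.

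**Working it through.** The protocol gives no dropout rate, SD, effect size, alpha or power, so there is no stated figure to reproduce. The point rests on a count from the text. The arithmetic after it is illustration only.

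**Count of contacts by arm**

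| | Art arm | Control arm |
|---|---|---|
| Sessions during the intervention, hence SMS occasions | 4 | 0 |
| Post-baseline times at which grief and anxiety are compared | 3 | 3 |
| Post-baseline times at which quality of life is compared (objectives) | 1 | 1 |
| Prompts described for any questionnaire | 0 | 0 |
| Optional later sessions | none | up to 2, volunteers only |

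The last row could add control SMS occasions before week 8 only if the shortened course ran before week 8 and the SMS covered it. The Summary's timing points against that. Even if both held, the messages would come after the interim and end-of-intervention forms and would reach volunteers only.

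**Illustrative bias (assumed inputs)**

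Let m be the fraction of forms missing in an arm, and g the difference in mean between responders and non-responders in SD units, taken as the same in both arms. The responders' mean differs from the full-arm mean by m × g. The between-arm comparison therefore shifts by (m_control − m_art) × g.

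- Assume 25% missing in controls and 10% in the art arm, a gap of 0.15.
- g = 0.5: 0.15 × 0.5 = 0.075 SD.
- g = 1.0: 0.15 × 1.0 = 0.15 SD.
- Wider range: a gap of 10 to 30 points with g from 0.3 to 0.8 gives 0.10 × 0.3 = 0.03 SD up to 0.30 × 0.8 = 0.24 SD.

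The direction follows the signs of the gap and of g. The documents fix neither.

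**Does the imbalance itself cost precision?**

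With unit SD, the standard error of the difference is sqrt(1/n1 + 1/n2). Power is for a two-sided 5% t-test at 0.736 SD, the difference that 30 per arm detects with 80% power (all assumed).

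| Women analysed | Standard error | Power |
|---|---|---|
| 30 and 30 | sqrt(2/30) = 0.258 | 0.80 |
| 27 and 22 (11 lost, uneven) | sqrt(1/27 + 1/22) = 0.287 | 0.709 |
| 25 and 24 (11 lost, even) | sqrt(1/25 + 1/24) = 0.286 | 0.713 |

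Losing 11 women costs nearly the same precision however the loss is split. The fall from 80% to about 71% is an effect of total loss. Only the bias term belongs to unequal response.

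**The case against.** Four objections have weight.

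First, a reader might infer that controls can never receive a reminder. The documents do not support that: a control who accepts the shortened course might be sent an SMS for it, and the two sections differ on when that course takes place. What stands is narrower. Controls have no session during the intervention, and on the Summary's wording none before the study period ends.

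Second, a reader might infer that controls are not seen or contacted at all. The protocol does not say so. It requires their interim and end-of-intervention forms, so some contact must occur, and an electronic form must reach each woman somehow. Chasing procedures may also sit in an operational document. The supportable statement is that no prompt is described. The protocol does, however, choose to name a remedy, and the one it names does not address questionnaire return.

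Third, a reader might count the electronic 8-week form as part of the difference between arms. It applies equally to both and may even ease response. The difference between arms lies only in the session SMS and the session contact.

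Fourth, a reader might infer that dropout will be worse in controls. That is not established. The art arm carries four 90-minute sessions in two weeks, and absence from all sessions is an exclusion criterion that can operate only there, so attrition could be higher in that arm and the reminders could offset it. The offer of later sessions may also keep controls in the trial. No figure in the protocol supports any particular gap.

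These objections limit the claimed consequence. They leave untouched the mismatch between the stated purpose of the SMS and what it does.

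**Conclusion.** The point holds as a weakness of design. The single measure named against loss to follow-up operates in one arm during the intervention (four occasions against none), is tied to attendance, and does not target outcome return. No questionnaire prompt is described in either arm.

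The consequence is a risk, not a demonstrated bias. On assumed values (a 15-point gap in missing forms, and a responder difference of 0.5 to 1.0 SD that is equal in both arms) the shift is 0.075 to 0.15 SD. That is about a quarter to a half of one standard error (0.075/0.287 = 0.26; 0.15/0.287 = 0.52). With no gap, and the same responder difference in both arms, it is zero. Power figures should not be cited as a cost of the asymmetry. Because prevention is simple and lost self-reports cannot be recovered, the change is worth making as a cheap improvement.

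**What to change.** Replace the loss-to-follow-up sentence in Implementation Method with wording such as: *Women in both arms receive the same SMS one day before every questionnaire (interim, end of intervention and 8 weeks), and the same repeat reminder if the form is not returned. Session-attendance messages for the art arm are separate and are not counted as a follow-up measure.* Add that questionnaire return will be reported by arm at each time.

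The two statements on when controls are offered the shortened course should also be reconciled, so that it is clear which contacts can precede the 8-week form.

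The cost is a few more messages and slightly more contact with controls than the protocol now describes. No extra staff are needed, and eligibility, treatment and endpoints are unchanged.
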